**Figure 4 F4:**
[figure not shown]
Session schedule.

## Stepwise procedures

### Preliminary app search

In August 2016 we conducted a preliminary search of unbundled speech therapy applications currently available on the iTunes store for the learning of English speech sounds by children aged 5 years of age and younger. None of the 44 apps returned by the search supplied feedback for the child's utterance. Nineteen apps relied entirely upon speech pathologists and others to provide feedback. Three apps provided feedback specifically to supplement human feedback. Feedback provided by 25 apps was predominantly verification feedback, which requires less informed judgment of the correctness of the utterance compared with elaborative feedback and consequently requires less complicated software. Fifteen apps provided KR feedback alone, and a further four provided KR in combination with other types of feedback. In summary, from the perspective of the literature discussed in this protocol, the apps returned by the search provide insufficient feedback to be of value during independent practice.

### Ethics

The protocol was approved by Swinburne University Human Ethics Research Committee: SHR Project 2017/262 on October 20 2017, in accordance with the National Statement on Ethical Conduct in Human Research (2007) and the Australian Code for the Responsible Conduct of Research. The assent of children participating will be sought as well as the consent of a parent or legal guardian as per the NHMRC National Statement Guideline 4.2.7.

The primary operational concern in conducting research into speech sound disorders is the ethical concern of using a non-standard or tested treatment with children. Speech pathology treatments should be characterized by beneficence and non-maleficence yet a non-standard treatment may be of no benefit and delay a child's access to beneficial treatment. The trial described in this protocol avoids these ethical concerns for several reasons. Firstly, the length of this trial is only 3 weeks which is shorter than average waiting list times for speech pathology services (Community Affairs References Committee, 2014) meaning that participation in the trial is unlikely to delay access to standard speech pathology intervention. Secondly, although the need for feedback in speech pathology intervention is accepted by clinicians and adopted into practice, the efficacy of feedback, let alone form or feedback, has not been established in the literature. Some of the treatment conditions in this protocol may expose children to non-standard feedback conditions but without an evidence base for standard practice, non-standard feedback conditions are no less appropriate to use. Thirdly, the treatment conditions proposed are based on sound principles of learning theory and speech pathology practice such that they may be of benefit and are highly unlikely to be of any harm. A final issue is that the control group could be perceived to be disadvantaged as they will not receive the experimental therapy nor traditional therapy during their participation. This is compensated by the fact that they will receive traditional therapy following their participation in the study.

### Feasibility and pilot study

We have a working HTML5 / JavaScript prototype which provides a) a practice game with images and sounds for three minimal pairs; and b) a demonstration game with KR feedback for a correct response for one minimal pair (Bee/Pea). The prototype is loaded onto a server from where it enables communication from a mobile device operated by a “Wizard” to a device operated by a child. The “Wizard of Oz” application will build on this prototype.

Once the application is developed, each option in the game will be tested in the Swinburne University BabyLab “Wizard of Oz” setting by the research team, including at least two speech pathologists. Once any revisions to the application are complete, the testing process will be repeated with four children aged four to six.

### Recruitment of participants

Potential participants will be identified from the Australian Catholic University Speech Pathology in Schools program in Melbourne. This program operates in several Catholic Education Primary Schools in Melbourne. Parents of clients of this service who are identified as having a phonological delay or disorder will be provided with an information sheet about the study. Parents who wish for their children to participate will be required to contact the staff of the study. Additional participants will be recruited through advertisement in kindergartens, day-care centers and playgroups.

Stratified random sampling based on severity of speech disorder and will be used to allocate children to experimental conditions. This process will ensure that each condition includes similar proportions of children with either a mild, moderate or severe phonological disorder. Due to the nature of the intervention, participants and therapists cannot be blinded to the experimental condition. However, pre- and post-test assessments of speech production will be carried out by a researcher/therapist blind to the assigned condition.

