## Materials and equipment

### Participants

Children aged between 4 and 6 with phonological delay or phonological disorder as identified by a qualified speech pathologist using the Developmental Evaluation of Articulation and Phonology (DEAP; Dodd et al., 2002) will be randomly allocated to five groups, each with 30 participants. Phonological delay is defined as the consistent use of phonological processes that are used in typical development that are supressed by 90% of children of the same chronological age (Dodd, 2014). Phonological disorder was defined as the consistent use of phonological processes in which some of the phonological processes used by that child are not used by 90% of children at any stage of their development (Dodd, 2014). The children will all consistently use one or more of the three phonological processes to be targeted by the intervention of this study (stopping, fronting or cluster reduction). The severity of each child's diagnosis will be either mild, moderate or severe with reference to the normative data for percentage consonants correct (PCC) as measured by the DEAP.

All children will be monolingual English speakers with receptive language within or above the expected range for their age as measured by the Clinical Evaluation of Language Fundamentals –Preschool 2nd Edition (Wiig et al., 2006) or Clinical Evaluation of Language Fundamentals –Fourth Edition (Semel et al., 2006). Children will have hearing skills within normal limits as measured by their last hearing test within the last 12 months and will not have other symptoms of developmental delay as reported by parents. The children will also have no apparent deficits in structure and function in oromotor structure and function as determined by examination by a speech pathologist.

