## Proposed analysis

The assessments of speech production will be transcribed to an Excel spreadsheet. Statistical analysis will be performed using the Statistical Package for the Social Sciences (IBM SPSS Statistics 24).

The key question to be addressed in this research is: How does feedback type during speech therapy session influence children's production performance. As such, the key dependent variable under analysis will be PCC, phonological process percentage of occurrence and percentage accuracy of trials. Published data of PCC in children's development (e.g., Dodd et al., 2002) suggest that this variable to be normally distributed. As such we intend to perform a full-factorial regression analysis on PCC with feedback condition, number of trials completed, and child age (4, 5, or 6 years) and severity as predictor variables. The full-factorial nature of this analysis will allow us to determine how the effects of condition and trials completed independently predict PCC and the extent to which these factors interact in their effects on PCC between pretest and post-test. For example, we may find that with certain types of feedback, the number of trials completed has a much greater effect than with other types of feedback. Similarly, we may find that some feedback types have a greater effect on performance for younger or older children. These analyses will also be completed with phonological process percentage of occurance at pretest and post-test and percentage accuracy of trials as a dependant variables

We will also conduct a Generalized Linear Model Analysis assuming a binomial distribution for the number of correct trials post “intervention” within a total of *n* trials where *n* may differ between children. The analysis will control for pre “intervention” language skills, age, and gender. Marginal means will be compared for the five groups using a Bonferroni correction for multiple comparisons. This analysis could assist in distinguishing the effects of real-world simulation vs. verification feedback and the presence of articulation guidance.

Motivation to persevere could be considered a variable that mediates the impact of type of feedback. Consequently, we will also perform a one-way ANOVA to determine how feedback condition influences motivation as measured by the number of trials and the duration of game play.

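### Diagnosis (delay or disorder) defines who is enrolled but is neither a stratification factor nor a term in any listed model, which costs a little precision and leaves a relevant moderator unexamined, without biasing the comparison

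*Protocol article*

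**What the plan says.** The Participants section of the protocol article describes the population as "Children aged between 4 and 6 with phonological delay or phonological disorder as identified by a qualified speech pathologist" and defines the two diagnoses separately. Delay means consistent use of processes that occur in typical development but that most children of that age have dropped. Disorder means that some of the child's processes are not part of typical development at any stage. Severity is a separate scale, graded on PCC norms: "The severity of each child's diagnosis will be either mild, moderate or severe". The children "will be randomly allocated to five groups, each with 30 participants".

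Allocation is described in Recruitment of participants: "Stratified random sampling based on severity of speech disorder and will be used to allocate children to experimental conditions", so that each condition has "similar proportions of children with either a mild, moderate or severe phonological disorder".

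Proposed analysis lists the terms of its models. The full-factorial regression uses "feedback condition, number of trials completed, and child age (4, 5, or 6 years) and severity as predictor variables", and is repeated for process percentage of occurrence and trial accuracy. The binomial model adjusts for pre-intervention "language skills, age, and gender". The ANOVA of motivation uses condition only. Research question 2 asks which variables affect how well each feedback type works.

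**The concern.** A factor that defines the population, and that a speech pathologist determines at entry with the DEAP, drops out at both places where it could be used. Severity does not replace it, because the protocol grades severity on a different scale.

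The protocol's own definitions give a reason why diagnosis could matter. The Stimuli section limits the targets to stopping, velar fronting and cluster reduction, all processes that most children over 3;11 have dropped. A child with disorder uses some atypical processes as well, and the game does not target those. PCC counts consonant errors whatever process causes them, and Outcome measurement leaves open whether there is any generalisation to other processes. The same success on the targets could therefore move PCC less in disorder than in delay.

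If so, diagnosis adds unexplained variation to PCC change, chance imbalance between arms goes unadjusted, and research question 2 is not examined for this factor.

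**Working it through.** **Is diagnosis in any stated allocation or model?**

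- Stratification: severity only.
- Regression: condition, number of trials, age, severity.
- Binomial model: pre-intervention language skills, age, gender.
- ANOVA: condition.

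Diagnosis is in none of them.

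**The plan's own figure.** Proposed analysis gives N = 150 for f = 0.32, 5% significance and 80% power. By the noncentral F method (noncentrality N × f²), a one-way ANOVA with 5 groups needs N = 122, or 125 with equal groups, and N = 150 gives 88.8% power. The figure of 150 is not reproduced this way, but it errs on the safe side and the present point does not depend on it. It shows only that there is room for an extra covariate.

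**Chance imbalance between two arms.** The input is n = 30 per arm (Participants). The share p of one diagnosis is not given, so a range is assumed, with diagnosis taken as unrelated to severity. The 95% range is ±1.96 × √(2p(1−p)/30):

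- p = 0.5: 1.96 × 0.129 = 0.253, about ±25 points
- p = 0.3: 1.96 × 0.118 = 0.232, about ±23 points
- p = 0.2: 1.96 × 0.103 = 0.202, about ±20 points
- p = 0.1: 1.96 × 0.077 = 0.152, about ±15 points

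**Spread across all five arms.** This comes from a simulation of five Binomial(30, p) arms with 400,000 draws:

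| Share p | Highest minus lowest arm ≥ 20 points | Median gap (points) | 95th percentile (points) |
|---|---|---|---|
| 10% | 11% of trials | 13 | 20 |
| 20% | 38% | 17 | 27 |
| 30% | 53% | 20 | 33 |
| 50% | 61% | 20 | 33 |

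**What an imbalance would do to a contrast.** Assume that mean PCC change differs by 0.5 SD between diagnoses; the protocol gives no such figure.

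- Edge of the 95% range at p = 0.5: 0.25 × 0.5 = 0.125 SD
- One standard deviation of imbalance: 0.129 × 0.5 = 0.065 SD
- Standard error of an unadjusted two-arm difference: √(2/30) = 0.258 SD

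The extreme case is thus about half a standard error (0.125/0.258 = 0.48), and the typical case about a quarter (0.065/0.258 = 0.25).

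**What adjustment would gain.** On the same assumption, diagnosis explains 0.5 × 0.5 × 0.5² = 0.0625 of the variance. The standard error falls by the factor √(1 − 0.0625) = 0.968, about 3%. A covariate explaining 5% of variance would raise power at N = 150 and f = 0.32 from 88.8% to 90.5%.

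**What the added terms would cost.**

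- Main effect: 2 − 1 = 1 df. The required N stays at 122.
- Interaction with condition: (5 − 1) × (2 − 1) = 4 df. At f = 0.32, N = 150 and equal numbers per diagnosis, power is 88.8%. That f is large for an interaction, because the difference between diagnoses would have to vary across conditions by about 2 × 0.32 = 0.64 SD (root mean square). If one diagnosis had a 10% share, there would be only 150 × 0.1/5 = 3 such children per arm.
- Diagnosis inside the full factorial: condition × age × severity already has 5 × 3 × 3 = 45 cells (150/45 = 3.3 children each), and diagnosis would make 90 (1.7 each).

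**The case against.** The strongest reply is that nothing here is wrong in the strict sense. Stratifying on severity alone is a legitimate choice, chance imbalance does not bias a randomised comparison, and the standard error already allows for it. This stands in full. A reader might infer that the arm comparisons are biased, or that a shift of about 0.13 SD is to be expected. Neither is supported: that shift multiplies an edge-of-range imbalance by an assumed effect.

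Second, the protocol never says that the diagnoses respond differently. The Introduction holds that minimal pair therapy can resolve both, every child must use at least one targeted process consistently, and Anticipated results names age and severity as examples of influences. This also stands, so the mechanism remains an inference.

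Third, process occurrence and trial accuracy are analysed as well, and they follow the targets more closely than PCC does. That limits the concern mainly to PCC.

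Fourth, further covariates may be left to a statistical analysis plan that is not shown. This has some force, but the article lists its predictors explicitly and diagnosis is not among them.

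Fifth, research question 2 is open-ended and does not name diagnosis. A reader might infer that the question goes unanswered, or that diagnosis is the only clinical feature recorded. Neither holds: age, severity, trials and motivation are analysed, and receptive language, stimulability and earlier therapy are recorded too. Nor does the wording on stratification suggest that children with delay are left out, since the same section recruits both diagnoses.

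**Conclusion.** The point holds in a limited form. Two separately defined diagnoses are enrolled, and diagnosis appears in neither the stratification nor any listed model. The comparisons remain unbiased. The loss is about 3% in standard error if the diagnoses differ by 0.5 SD and are equally common, unadjusted chance imbalance of up to about ±23 to ±25 points between two arms at shares of 30 to 50%, and a relevant moderator left unexamined. These sizes rest on an assumed diagnosis mix, an assumed effect, and no association between diagnosis and severity. Any association would mean that the existing stratification already balances diagnosis in part. It is worth correcting because the correction is nearly free, not because the planned comparisons are unsound.

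**What to change.** Add diagnosis (delay or disorder) as a main-effect covariate in the PCC and process-occurrence models, and state that it stays outside the full factorial. Report one condition-by-diagnosis interaction, labelled exploratory, under research question 2, with estimates and confidence intervals.

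The cost is 1 df for the main effect and 4 for the interaction, 5 in all. No new data are needed, since diagnosis is determined at entry. The interaction will be imprecise if one diagnosis is rare, and the report should say so.

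Stratifying allocation by diagnosis as well as severity is optional. It gives 2 × 3 = 6 strata, on average 150/6 = 25 children each, or 5 per arm, and some strata may be much smaller. If that is too fine, the covariate alone is enough.

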## Proposed analysis

The assessments of speech production will be transcribed to an Excel spreadsheet. Statistical analysis will be performed using the Statistical Package for the Social Sciences (IBM SPSS Statistics 24).

The key question to be addressed in this research is: How does feedback type during speech therapy session influence children's production performance. As such, the key dependent variable under analysis will be PCC, phonological process percentage of occurrence and percentage accuracy of trials. Published data of PCC in children's development (e.g., Dodd et al., 2002) suggest that this variable to be normally distributed. As such we intend to perform a full-factorial regression analysis on PCC with feedback condition, number of trials completed, and child age (4, 5, or 6 years) and severity as predictor variables. The full-factorial nature of this analysis will allow us to determine how the effects of condition and trials completed independently predict PCC and the extent to which these factors interact in their effects on PCC between pretest and post-test. For example, we may find that with certain types of feedback, the number of trials completed has a much greater effect than with other types of feedback. Similarly, we may find that some feedback types have a greater effect on performance for younger or older children. These analyses will also be completed with phonological process percentage of occurance at pretest and post-test and percentage accuracy of trials as a dependant variables

We will also conduct a Generalized Linear Model Analysis assuming a binomial distribution for the number of correct trials post “intervention” within a total of *n* trials where *n* may differ between children. The analysis will control for pre “intervention” language skills, age, and gender. Marginal means will be compared for the five groups using a Bonferroni correction for multiple comparisons. This analysis could assist in distinguishing the effects of real-world simulation vs. verification feedback and the presence of articulation guidance.

Motivation to persevere could be considered a variable that mediates the impact of type of feedback. Consequently, we will also perform a one-way ANOVA to determine how feedback condition influences motivation as measured by the number of trials and the duration of game play.

A G-Power power analysis suggested a total sample size of 150 in order to detect a moderate to large effect size (*f* = 0.32) with 5% significance and 80% power. Our recruitment plan of 30 participants in each of our 5 conditions is consistent with the G-Power analysis suggestion to avoid type II error.

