### Outcome measurement

The relative benefits of the different experimental conditions will be measured by the primary measure of changes in use of phonological processes and PCC from pre-test to post-test as measured by the DEAP (Dodd et al., 2002). Such assessment will capture suppression of the phonological processes targeted in treatment and generalization effects (if any) to other phonological processes. Phonological process percentage of occurance (Randolph and Wendt, 2014; i.e., the number of times that a child uses a given phonological process) will also be measured and compared pre and posttest. Pre and post-test assessments will be recorded and a sample of the assessments independently analyzed followed by interrater reliability checks. In addition to the pre-test/post-test measures, number of trials and percentage accuracy of trials per session (cumulative accuracy) will be measured for each experimental condition as further indication of the effectiveness of feedback of that condition and determine when goals of intervention have been reached. For example, if a child reaches 90% accuracy of production of target words for one phonological process, another will be targeted. It could be argued that motivation to continue playing will increase practice and consequently improve outcomes (Williams, 2012). A secondary measure of motivation as a variable that could influence the effectiveness of feedback type will be the amount of time participants choose to continue playing the game (Deci et al., 1999) up to a total of 20 min as well as the number of trials they complete.

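### Three unranked key outcomes each go into a full-factorial model too sparse for 150 children, with no error control stated across outcomes or effects in those models

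*Protocol article*

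**What the plan says.** The Outcome measurement section defines a "primary measure of changes in use of phonological processes and PCC from pre-test to post-test". It introduces trial accuracy as something measured in addition to the pre/post assessments. The Proposed analysis section is broader: "the key dependent variable under analysis will be PCC, phonological process percentage of occurrence and percentage accuracy of trials". It ranks none of the three.

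The model for PCC is described as follows: "full-factorial regression analysis on PCC with feedback condition, number of trials completed, and child age (4, 5, or 6 years) and severity as predictor variables". It is then extended: "These analyses will also be completed with phonological process percentage of occurance at pretest and post-test and percentage accuracy of trials as a dependant variables". Interactions are part of the purpose. The section gives condition by trials and condition by age as examples of what may be found.

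The same section states a Bonferroni correction, but for the five-group marginal means of a separate binomial model. The sample size statement gives a single error level, "with 5% significance and 80% power", without naming the outcome or effect it refers to. The plan is for "30 participants in each of our 5 conditions".

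**The concern.** A full-factorial model uses up information quickly. With three categorical factors and a crossed covariate, 150 children are spread over many cells, and some cells may hold nobody. With empty cells, a main effect of condition taken from the full model no longer estimates one clear average difference between feedback types. What it estimates depends on which cells are empty and on how the software handles them. That matters because the effect of feedback type is the trial's key question.

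The second problem is error control. Three outcomes, each with many testable effects and none ranked first, leave open which test decides the question. The 5% in the power statement then does not describe the set of tests the plan sets up.

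**Working it through.** **The plan's own figure.** Inputs are f = 0.32, alpha 0.05, power 0.80 and five groups (Proposed analysis). A one-way ANOVA with noncentrality f² × N = 0.32² × 150 = 15.36 and 4 numerator df has power 0.888 at N = 150. It reaches 80% at N = 122, or 125 in equal groups. The stated 150 is therefore not reproduced, but the gap is on the safe side.

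**Size of the model.**
- Condition has 5 levels, age 3 (4, 5, 6 years) and severity 3 (mild, moderate, severe): 5 × 3 × 3 = 45 cells, and 150/45 = 3.3 children per cell.
- A trials slope in every cell gives 45 × 2 = 90 coefficients and 150 − 90 = 60 residual df.
- Controls do not play (Abstract; Table 4), so the 3 × 3 = 9 control-arm slopes cannot be estimated: 90 − 9 = 81.
- Trial accuracy exists only in the four playing arms: 4 × 3 × 3 = 36 cells and 4 × 30 = 120 children, again 3.3 per cell.

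**Empty cells.** The documents give no age or severity distribution, so two mixes are assumed.

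| Assumed mix | Expected empty cells | Cells with 0 or 1 child | Chance of any empty cell |
|---|---|---|---|
| Even: severity 10/10/10 per arm, ages one third each | 0.8 | 4.7 | 55% |
| Skewed: severity 12/12/6 per arm, ages 45/40/15% | 3.7 | 10.6 | 99% |

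The even row follows by hand. A given age is missing from a stratum of 10 with probability (2/3)^10 = 0.0173, and 45 × 0.0173 = 0.78. The chance that some age is missing from a stratum is 3 × (2/3)^10 − 3 × (1/3)^10 = 0.052. Over 15 strata this gives 1 − 0.948^15 = 0.55.

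**Error rates**, if every null is true and tests are independent (1 − 0.95^m):
- condition on two primaries: 1 − 0.95² = 9.75%
- condition on three outcomes: 1 − 0.95³ = 14.3%
- all effects: four predictors give 2⁴ − 1 = 15 effects per model, 15 × 3 = 45 tests, and 1 − 0.95^45 = 90.1%.

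The outcomes come from the same children, so independence is an upper case. A null simulation of all 45 effects gave about 44% to 84%, depending on the correlation between outcomes (0 to 0.8) and the type of sums of squares. For simplicity it gave every child a trial count, controls included.

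**Power at f = 0.32, N = 150** (noncentral F, 45-cell model): 0.78 for an 8-df interaction such as condition by age, and 0.61 for the 16-df condition by age by severity term. For condition, the same formula gives 0.87-0.88, but it adjusts only the residual df and ignores unequal and empty cells. When the Type III condition test was simulated in the 45-cell model without trials (equally spaced arm means), power was about 0.7 under the even mix and about 0.3 under the skewed one. A main-effects model kept about 0.86 to 0.89.

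**The case against.** Several points on the other side stand.

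- A Bonferroni correction is stated for the five-group comparison in the binomial model, so it would be wrong to say the plan has no error control. The gap is confined to the factorial models.
- The Outcome measurement section gives a partial ranking, with process use and PCC as primary. Read that way, the error for condition is at most about 10%.
- A reader might infer that cells are nearly empty. The mean of 3.3 does not support that. With an even spread, less than one of the 45 cells is expected to be empty, so the cells are sparse, with some empty or single-child cells. If age were entered as a number, there would be 5 × 3 = 15 condition by severity cells of 10 on average.
- A reader might also infer that a false finding is close to certain. The 90% needs all 45 effects read at 5%, every null true, and independence. The key question is one condition test per outcome.
- Power of 0.78 for an 8-df interaction is close to the 80% target, so two-way interactions are not hopeless at the stated effect size.

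One might add that an article leaves detail to an analysis plan. That does not answer the point, because the article itself fixes the full-factorial form and the three key outcomes. Nor does the 0.87-0.88 for condition rescue the model, since that formula takes no account of unequal and empty cells.

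**Conclusion.** The concern holds in a limited form. The plan commits three unranked key outcomes to a model that is too sparse for 150 children. With trials crossed, the five-arm version cannot be fitted as written, and no error control is stated across outcomes or effects in these models.

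For condition alone, the chance of a false positive is up to about 10% on two primaries and 14% on three outcomes. It reaches 44-90% only if every effect is read at 5%. The sparsity figures rest on age being a three-level factor, on no dropout, and on assumed age and severity mixes. The loss of power for condition also depends on the Type III choice.

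The documents do not support the stronger readings that the cells are nearly empty, that a false finding is nearly certain, or that the trial is too small for its stated effect. With a simpler model, 150 children are enough.

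**What to change.** 1. Name one primary outcome. Post-test PCC is the natural choice, since the model is written for it. Alternatively, take PCC and process occurrence as co-primaries under Holm. Make trial accuracy secondary.
2. Make the primary analysis a main-effects model of condition, severity stratum, age and pre-test value. Leave out trials completed, which controls do not have. At N = 150, with f = 0.32 relative to the model's residual SD, power is 0.888 for one primary test and about 0.82 at alpha 0.025. Keeping all three outcomes under Bonferroni (0.05/3 = 0.0167 each) would give 0.781, just short of the stated 80%.
3. Keep condition by age, condition by severity and, in the four playing arms only, condition by trials as pre-named exploratory tests, fitted one at a time. This keeps the condition by trials question that the protocol raises.
4. Drop the higher-order terms.

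This changes analysis wording only. It needs no extra children and no change in conduct. The cost is fewer interaction claims, with those kept labelled exploratory. The choice of primary outcome must be made before post-test data are seen.
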